#### Control of bias and confounding

Potential confounders (hospital organization, influence of individual doctors, local conditions affecting care, and resources) are controlled by randomization. However, since cluster randomization may result in imbalances of baseline differences, these variables are also documented and analyzed.

Through the use of standardized questionnaires, the possibility of information bias is reduced.

It should be considered that support needs could be awakened by participation in this study. For this reason, questions are asked before and after the doctor’s conversation in order to be able to identify possible changes. However, since screening for psychosocial stress is required in all cancer patients according to the German guideline on psycho-oncological diagnostics and treatment, we do not consider it ethically justifiable to establish a third study arm that does not ask about the burden and the care desired.

#### Statistical analysis

The analysis of the primary outcome “proportion of adequate care for patients with increased psychosocial stress” will be based on hierarchical models for cluster-randomized studies (with random intercept for the clinics).

Due to the limited number of clinics, the following variables will also be adjusted: sex, age, ECOG stage, initial or recurrent disease, neurological deficit, time since initial diagnosis, living alone vs in partnership. The analyses are performed according to intent to treat. The aim is to reduce a possible bias by selective drop-out. The secondary endpoints are also calculated using mixed models.

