**Fig. 1 Fig1:**
[figure not shown]
Course of the study

The clusters are the institutions (hospitals) participating in this trial (*n* = 13). In intervention arm hospitals, distress is assessed within the doctor–patient consultations. In CAU hospitals distress is assessed with the DT.

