#### Sample size

Based on previous studies [21] we expect that in the control group only about 15% of mentally stressed patients receive psychosocial care compared to an expected 25% in the intervention group.

Due to the fact that this is a cluster-randomized study, more patients have to be included in the study.

The sample size calculation is based on recommendations by Hayes and Bennett, who developed several scenarios for cluster-randomized studies and provided formulas for the calculation of the cluster effect. The intracluster correlation coefficient (ICC) in a comparable, cluster-randomized study with 13 clusters was between 0.03 and 0.19 depending on the outcome [21]. However, Donner and Klar (2004) warn of overestimating the stability and size of an ICC. Therefore, we assume an ICC of 0.005. We further assume that 50 patients will be included in the study in each clinic and that the clusters will be of the same size. In this scenario (ICC 0.005), 12 clinics with a total of *n* = 616 patients are required to demonstrate the expected intervention effect (25% vs 15%) with α of 0.05 and a power of 80%.

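### The 80% power makes no allowance for only 12 to 13 clinics: a test on 10 to 11 degrees of freedom has about 70 to 73% power even at ICC 0.005, and the clinic counts do not agree

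*Protocol article*

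**What the plan says.** The Sample size section expects that "only about 15% of mentally stressed patients receive psychosocial care" in the control arm, "compared to an expected 25% in the intervention group". It reports ICCs of 0.03 to 0.19 from a comparable 13-cluster trial but adopts 0.005. On cluster size it says: "We further assume that 50 patients will be included in the study in each clinic", with all clusters equal. From this it concludes that "12 clinics with a total of" 616 patients are needed, "with α of 0.05 and a power of 80"%.

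The abstract, the Setting section and the text under Fig. 1 all give 13 clinics. The last defines the units of randomisation: "The clusters are the institutions (hospitals) participating in this trial".

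Under Statistical analysis, the primary outcome "will be based on hierarchical models for cluster-randomized studies (with random intercept for the clinics"). The section then says: "Due to the limited number of clinics, the following variables will also be adjusted". The variables listed are all patient-level: sex, age, ECOG status, initial or recurrent disease, neurological deficit, time since diagnosis and living situation. No reference distribution or degrees of freedom for the arm effect is given.

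**The concern.** Treatment is assigned to hospitals, so the arm comparison is judged against variation between hospitals. With 12 or 13 of them, that variation is estimated on only 10 or 11 degrees of freedom. A calculation with normal quantiles treats it as known.

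One of two prices is then paid. Either the test allows for the few clinics and has less power than stated, or it does not and the nominal 5% may be exceeded. The first means a real improvement in access to psychosocial care is more likely to be missed than the plan implies. The second means a positive result is weaker evidence than its p-value suggests.

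**Working it through.** **Inputs** (Sample size section): p0 = 0.15, p1 = 0.25, α = 0.05 (sidedness not stated; two-sided reproduces the total), power 80%, ICC 0.005, m = 50 per clinic. Assumed here: 13 clinics split 6 versus 7, since the split is not given; equal clinic sizes; and all 616 patients counted in the primary comparison, as the plan's own calculation does.

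**Step 1: reproduce the plan's figure.**
- Per arm, individually randomised: (1.960 + 0.842)² × (0.15 × 0.85 + 0.25 × 0.75) / 0.10² = 7.849 × 0.315 / 0.01 = 247.24
- Design effect: 1 + (50 − 1) × 0.005 = 1.245
- Per arm: 247.24 × 1.245 = 307.8, so 308; total 616

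The match is exact, so no small-cluster allowance is contained in 616.

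**Step 2: clinic counts.** 12 × 50 = 600, not 616. 616 / 50 = 12.3 clinics; 616 / 12 = 51.3 per clinic; 616 / 13 = 47.4 per clinic. Thirteen clinics cannot be divided equally between two arms.

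**Step 3: power with a t reference at ICC 0.005.** SE² = DE × (0.1275 / n0 + 0.1875 / n1), with DE = 1 + (m − 1) × 0.005. The non-centrality is 0.10 / SE and the degrees of freedom are clinics minus 2. For 12 × 50: SE² = 1.245 × 0.315 / 300 = 0.001307, SE = 0.0362, non-centrality 2.77, critical value 2.228.

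| Design | df | Power, normal | Power, t |
|---|---|---|---|
| 12 clinics, 600 patients | 10 | 79.0% | 70.3% |
| 12 clinics, 616 patients | 10 | 79.8% | 71.2% |
| 13 clinics, 616, 7 in control | 11 | 79.6% | 71.9% |
| 13 clinics, 616, 7 in intervention | 11 | 80.8% | 73.1% |
| 13 clinics × 50 = 650, 7 in intervention | 11 | 82.4% | 75.0% |

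At 50 per clinic, the t-based power is 78.3% with 7 clinics per arm and 84.3% with 8.

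**Step 4: simulation.** Clinic rates were beta-distributed, and a random-intercept logistic model was fitted by maximum likelihood without covariates, with 2,000 to 3,000 runs per scenario. Type I error is for 13 clinics of 47 with a 15% rate in both arms.

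| Quantity | Wald z | Same model, t on 11 df | Cluster-level t-test |
|---|---|---|---|
| Type I error, ICC 0.005 | 5.9% | 3.6% | 5.2% |
| Type I error, ICC 0.03 | 8.5% | 5.6% | 4.9% |
| Type I error, ICC 0.10 | 10.4% | 6.7% | 4.3% |
| Power, 15% vs 25%, ICC 0.005 | 79.9% | 72.1% | 71.9% |

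A separate simulation with a 20% event rate (1,500 runs) gave 5.3% at ICC 0.005 and 8.2% at ICC 0.03 for the Wald z test. The Monte Carlo standard error near 5% is about 0.4 points with 3,000 runs and 0.6 with 1,500.

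**The case against.** The strongest objection concerns type I error. The article names neither a Wald z test nor any degrees of freedom. A correction could sit in the analysis plan, which is not shown, and a condensed article may leave it there. A reader might infer that the primary test will be too liberal, but the document does not establish that. This stands, and the point is conditional.

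A reader might also infer that power is about 73% and the test is liberal at the same time. These are alternatives. An uncorrected z test keeps about 80% power; a corrected test holds its level and loses power.

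Third, inflation at the plan's own ICC of 0.005 is slight, and 5.3% in 1,500 runs cannot be told from 5%. Comparing 1.96 with a t-distribution on 11 df would suggest 7.6%, which overstates what the model does at that ICC. This also stands: clear inflation needs an ICC of 0.03 or more.

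Fourth, part of the lost power could come from the correction, because a t reference on the mixed model is conservative at ICC 0.005 (3.6%). This stands only in part: the cluster-level t-test holds its level there (5.2%) and still has about 72% power.

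Fifth, the covariate adjustment is best read as a response to chance imbalance, which the section on bias and confounding raises. That is a fair reading, so the adjustment is not a mistaken correction. It simply leaves degrees of freedom untouched.

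Finally, 50 may be a rounded planning value and the thirteenth clinic a margin. A 6 versus 7 split costs only about 0.6% in efficiency (1 − (1/13)² = 0.994). So the mismatch in counts is small, but the text as printed does not add up.

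**Conclusion.** The point holds in a limited form. The 80% power comes from a normal approximation with no allowance for few clusters. On the plan's own assumptions, a test with 10 to 11 degrees of freedom has about 70 to 73% power: 70% for 12 × 50, 71% for 616 in 12 clinics, and 72 to 73% for 616 in 13 clinics with an assumed 6 versus 7 split. An unseen analysis plan cannot rescue the stated figure, because if it does correct the degrees of freedom, the 80% no longer describes the planned test.

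If the test is left uncorrected, power is near 80%. Type I error is then about 5 to 6% at ICC 0.005 and about 8 to 9% at 0.03, the bottom of the range the Sample size section reports. Whether this applies depends on a choice the article does not state. The figures assume equal clinic sizes and no covariates.

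The choice of ICC is a separate and larger threat to power. At 0.03, t-based power is 43 to 46% for the 12- and 13-clinic designs with 600 to 616 patients.

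**What to change.** - Restate power for the 13 clinics randomised, giving the split by arm and using a t-distribution with clinics minus 2 degrees of freedom.
- Reconcile 12 clinics × 50 = 600 with 616 patients and 13 clinics.
- State how the arm effect is tested, using a small-sample reference suited to a binary mixed model, for example between-within degrees of freedom (11 for 13 clinics). Corrections developed for linear mixed models may require a different estimation method here, so they are not a like-for-like option.
- Add a covariate-adjusted cluster-level t-test as a sensitivity analysis. Keep the planned covariate adjustment for baseline imbalance.

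No new patients or data are needed. The cost is a lower stated power, confidence intervals about 12% wider (2.201 / 1.960 = 1.12), and a slightly conservative mixed-model test if the ICC really is as low as 0.005.

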### Primary and secondary endpoints

The primary endpoint is the proportion of patients with increased psychosocial stress who receive professional support from psychosocial services (psycho-oncology, social services, cancer counseling centers, palliative care with psychosocial support).

Secondary endpoints are number of patients reporting psychosocial stress; number of patients receiving psychosocial care through specialized services such as psycho-oncology, social services, cancer counseling centers, palliative care, etc.; number of patients referred to care structures; quality of life; need for support; psychological well-being and burden of the patients before and after doctor–patient consultation; and duration of the doctor–patient consultation.

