#### Conditions of the intervention arm

Psychosocial distress is measured by three questions that emerged as important in a preliminary study. The three questions are:
Has your mood worsened due to the disease?Do physical changes due to the disease, such as numbness, weakness, or feeling exhausted more quickly, put a strain on you?Has your mental capacity worsened as a result of the disease, making it harder for you to concentrate or remember things, for example?

On the basis of the patient’s answers, the doctor offers psychosocial care, if indicated and desired by the patient, and refers the patient to the appropriate specialist services, e.g., psycho-oncological service, clinic social service, outpatient cancer counseling centers, physiotherapy, established psychotherapists, etc.

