#### Conditions of the control arm

In the control arm, psychosocial distress is assessed using the DT, which can be evaluated within a few minutes, so that the results in the control group can also be discussed during the doctor–patient consultation. If there is an obvious need for treatment or if a patient requires psychosocial support, the referral is carried out analogously to the intervention condition.

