### Instruments applied in the study

#### Before the doctor–patient consultation, t1

First patients complete a baseline questionnaire (t1) assessing use of and wish for psychosocial support using an adapted version of a self-developed questionnaire [17]. Further, the European Organization of Research and Treatment of Cancer Core Questionnaire (EORTC QLQ-C30) with its brain module (BN20) will be applied. It is a self-assessment tool to evaluate cancer patients’ quality of life. Validity and reliability have been previously tested in several clinical studies [18].

Patients in the control group complete additionally the DT. This is a self-reporting screening instrument, measuring psychosocial distress by a numerical rating scale accompanied by a 40-item list with problems from different areas of life, e.g., practical, family, emotional problems, etc. [5, 19].

Afterwards, the patients have the doctor–patient consultation. In the intervention group, the three questions, described above, are asked during doctor–patient consultation instead of using the DT (Table 1).

**Table 1 Tab1:** Operationalization of the outcomes and measurement points shown by outcomes

Outcome	Measure	t1	t2	t3
*Primary outcome: Psychosocial care through specialized services*				
Inpatient psycho-oncological service	Operation and procedure codes in the clinic information system or self-developed questionnaire			x
Cancer Counseling Center	Self-developed questionnaire			x
Inpatient social service	Operation and procedure codes in the clinic information system or self-developed questionnaire			x
Outpatient psychotherapy	Self-developed questionnaire			x
Neuropsychology	Medical records or operation and procedure codes in the clinic information system			x
Rehabilitation	Self-developed questionnaire or data derived from medical records			x
*Secondary outcomes*				
Percentage of patients that can be assessed for psychosocial distress	Participation rate in intervention arm vs control arm		x	
Length of doctor–patient consultation	In minutes (documentation by clinicians in the study worksheet)		x	
Emotional functioning/distress	EORTC QLQ-C30, emotional functioning scale	x		x
Health-related quality of life	EORTC QLQ-C30, global scale and BN20, all scales	x		x
Support requested	Self-developed questionnaire	x	x	x
Appointments arranged in specialized services	Documentation by clinicians in the study worksheet		x	

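### The primary model omits the wish for support recorded before the consultation, although referral depends on it and few unblinded clusters may differ on it

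*Protocol article*

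**What the plan says.** The protocol article defines the primary outcome under Primary and secondary endpoints as the "proportion of patients with increased psychosocial stress who receive professional support from psychosocial services". Under Conditions of the intervention arm, "the doctor offers psychosocial care, if indicated and desired by the patient". Under Conditions of the control arm, "the referral is carried out analogously to the intervention condition". The patient's wish is therefore part of the route to care in both arms.

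The wish is measured before that route begins. The section on t1 states: "First patients complete a baseline questionnaire (t1) assessing use of and wish for psychosocial support". Table 1 marks support requested at t1, t2 and t3.

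The Statistical analysis section specifies a hierarchical model with a random intercept for clinic. It adds that "the following variables will also be adjusted: sex, age, ECOG stage, initial or recurrent disease, neurological deficit, time since initial diagnosis"; the seventh and last variable is whether the patient lives alone or with a partner. The reason given is the small number of clinics. Control of bias and confounding accepts that randomizing clusters may leave baseline differences. The t1 wish is not among the seven variables.

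**The concern.** A baseline covariate is worth having in a model when it predicts the outcome well and may be unbalanced. The t1 wish for support probably meets both conditions.

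- **Prediction.** Referral requires that care is wanted, so patients who want it beforehand should receive it more often than those who do not.
- **Imbalance.** Thirteen hospitals are randomized and the study is not blinded (Study design). Staff at each center screen and approach patients (Screening and informed consent procedure), and each clinic runs one arm only (Risk factors and control procedures). Staff and patients can therefore behave differently by arm at recruitment, for example if patients open to talking about distress enroll more readily in one arm. Randomizing hospitals does not prevent this. The random intercept carries chance variation between clinics into the standard error, but it does not remove a systematic recruitment difference.

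The plan's own reasons for adjusting apply to this variable at least as well as to several that are listed. The article names the list, so this is a stated choice and not a detail left open. At stake are precision and protection of the primary comparison.

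**Working it through.** **The plan's own figure.** Inputs from Sample size: 15% vs 25%, α 0.05 (two-sided fits), power 80%, 50 patients per clinic, ICC 0.005.

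- Per arm without clustering: (1.960 + 0.842)² × (0.15×0.85 + 0.25×0.75) / 0.10² = 247.24.
- Design effect: 1 + 49×0.005 = 1.245.
- Total: 2 × 247.24 × 1.245 = 615.6, i.e. 616. The stated figure reproduces.

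The 15% and 25% are stated as rates of receiving care, so they are already net of patients who decline. Nothing below changes 616.

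**Effect of an imbalance in t1 wish.** Let w be the share of distressed patients wishing support at t1, u₀ the uptake among those who do not, and u₁ the uptake among those who do. Only the 15% comes from the protocol. The ranges for w (30–60%) and u₀ (2–5%) are assumptions.

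- u₁ = (0.15 − (1 − w)u₀) / w
- Shift from a 10-point imbalance, with no true effect: 0.10 × (u₁ − u₀)
- Share of control-arm outcome variance explained: R² = w(1 − w)(u₁ − u₀)² / (0.15×0.85 = 0.1275)

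| w | u₀ | u₁ | Shift (points) | R² |
|---|---|---|---|---|
| 0.30 | 0.02 | 45.3% | 4.3 | 0.31 |
| 0.30 | 0.05 | 38.3% | 3.3 | 0.18 |
| 0.40 | 0.05 | 30.0% | 2.5 | 0.12 |
| 0.60 | 0.02 | 23.7% | 2.2 | 0.09 |
| 0.60 | 0.05 | 21.7% | 1.7 | 0.05 |

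The shift is 1.7–4.3 points against the planned 10, and R² is 5–31%. A second set of assumptions agrees in order of size. With 45% vs 55% wishing support, 30–50% of them receiving it and nobody else doing so, the shift is 0.10×0.30 to 0.10×0.50, i.e. 3–5 points.

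**How likely is a 10-point imbalance by chance?** Take w = 0.4, 308 patients per arm (generously treating all 616 as distressed) and 616/13 = 47.4 per clinic. The ICCs are those named under Sample size, applied to the wish by assumption. The SD of the arm difference is √[2×0.4×0.6/308 × (1 + 46.4×ICC)].

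| ICC | SD (points) | Chance of 10 points or more, either direction |
|---|---|---|
| 0.005 | 4.4 | about 2% |
| 0.03 | 6.1 | about 10% |
| 0.19 | 12.4 | about 42% |

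At ICC 0.005, a one-SD imbalance of 4.4 points shifts the comparison by 4.4×0.167 to 4.4×0.433, i.e. 0.7–1.9 points. These figures cover chance only. Differential recruitment would come on top, and the documents do not allow it to be quantified.

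**The case against.** The strongest reply is that nothing in the Statistical analysis section is wrong as written. The t1 wish precedes the consultation, so randomization balances it in expectation. A chance imbalance is sampling variation that the random intercept already reflects. At the planned ICC, 10 points is an imbalance of about 2.3 SD, and the wish and uptake shares are assumed. All of this stands, and it limits the point to precision and protection. It does not answer recruitment after allocation in an unblinded trial, and it gives no reason to leave out a predictor that is already collected.

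A reader might go further and infer that the primary endpoint treats patient preference as screening failure, because a distressed patient who was identified and declined scores the same as one who was missed. The Background encourages this by calling better identification the primary research question. The documents do not support that reading:

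- Objectives and hypothesis gives receipt of support its own hypothesis, and the endpoint section and Sample size also define the outcome as receipt. A patient who declines has not received care, so scoring no is the defined result.
- Screening accuracy against the SCID, referrals and appointments arranged, and support requested are separate secondary outcomes, so the steps can be told apart.
- Declining at the same rate in both arms leaves the ratio 25/15 = 1.67 unchanged and creates no false effect.

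A covariate would also not reclassify anyone who declined, and the t1 wish is not a decision to decline, since it comes before any offer. An analysis restricted to t1 wishers would drop patients whose needs are awakened later, which Control of bias and confounding expects. It would also drop those unable to complete the form, the very patients who motivate the trial.

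**Conclusion.** The point holds as a gap in the covariate list. The primary model leaves out a baseline variable that the referral rule makes likely to predict the outcome. Under the assumed shares, a 10-point imbalance would move the comparison by 1.7–4.3 points out of the planned 10, and the variable would explain about 5–31% of control-arm outcome variance. Both ranges rest on shares that the documents do not give. The imbalance itself is unlikely by chance at ICC 0.005 but plausible at 0.03–0.19 or with differential recruitment. The omission does not invalidate the comparison, the endpoint is not at fault, and 616 is unaffected. It should be corrected because the correction costs almost nothing and is credible only if made before the data are seen.

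**What to change.** Add the wish for support at t1 to the covariate list in the Statistical analysis section as a three-level factor: yes, no, form not completed. Leave the endpoint, the denominator and the sample size as they are.

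Do not adjust for the wish at t2. It is recorded after the consultation and may be part of the intervention's effect. For the same reason the t1 item should be answered before the control arm completes the Distress Thermometer, which is the order the t1 section describes. Any analysis restricted to patients who wished support at t1 should be labeled exploratory.

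The cost is a change of wording and one more model term (two parameters for three levels). No new data are needed. The small drawback is the category for missing forms, which will hold some of the more impaired patients. Adjustment removes only the part of a recruitment difference that shows in the stated wish.

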#### Follow-up, t3

Three months later, the patients will complete the EORTC QLQ-C30 + BN20 questionnaire and again an adapted version of the self-developed questionnaire (Table 1) in order to assess the proportion of patients receiving adequate care.

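### The primary model leaves out use of psychosocial support at t1, the baseline value of its own outcome, although the trial collects it

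*Protocol article*

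**What the plan says.** Under Primary and secondary endpoints: "The primary endpoint is the proportion of patients with increased psychosocial stress who receive professional support from psychosocial services". Table 1 marks every component of the primary outcome at t3 only. The Follow-up section says that the t3 questionnaire, three months on, is used "in order to assess the proportion of patients receiving adequate care". None of these places says that the care must have started after the consultation, or that patients already in care are set aside.

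The same kind of information is collected at the start. The section on t1 has a "baseline questionnaire (t1) assessing use of and wish for psychosocial support".

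The Statistical analysis section specifies a hierarchical model with a random intercept per clinic and then states: "Due to the limited number of clinics, the following variables will also be adjusted". The seven are "sex, age, ECOG stage, initial or recurrent disease, neurological deficit, time since initial diagnosis, living alone vs in partnership".

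Control of bias and confounding names hospital-level factors (organization, individual doctors, local conditions, resources) as controlled by randomization and adds: "However, since cluster randomization may result in imbalances of baseline differences, these variables are also documented and analyzed". That sentence concerns hospital factors, not each patient's use of support at t1.

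**The concern.** Where an outcome is also measured at baseline, the baseline value is usually among its best predictors, and it is the natural first covariate when few clusters are randomized. The article gives the right reason for adjusting but omits this variable from an explicit list, so the omission is a stated choice and not a detail left open.

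Prior care is plausible here. Patients are enrolled at first diagnosis, in follow-up and at recurrence (Risk factors and control procedures), and the article says the German guideline requires distress screening in all cancer patients. Some patients will probably have been screened and referred before t1. If that care continues to t3 and is counted, it says nothing about which assessment method worked better. If clinics differ in how much of it they provide, the difference enters the between-clinic variance. The random intercept allows for that variance in the standard error but does not remove it. A covariate could remove part of it.

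**Working it through.** **1. The plan's own figure.** Inputs from Sample size: 15% vs 25%, α 0.05 (two-sided assumed, since this reproduces the total), power 80%, ICC 0.005, 50 patients per clinic.

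- n per arm = (1.960 + 0.842)² × (0.15×0.85 + 0.25×0.75) / 0.10² = 247.24
- design effect = 1 + 49 × 0.005 = 1.245
- total = 2 × 247.24 × 1.245 = 615.6, i.e. the stated 616

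**2. How far the design depends on between-clinic variance.** Same formula, 616 patients, 50 per clinic:

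| ICC | Design effect | N for 80% power | Power at 616 |
|---|---|---|---|
| 0.005 | 1.245 | 616 | 80% |
| 0.01 | 1.49 | 737 | 73% |
| 0.02 | 1.98 | 980 | 60% |
| 0.03 | 2.47 | 1222 | 51% |

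**3. What varying prior use could add.** The article gives no t1-use rate and no spread, so everything in this step is assumed. Let a share b of patients be in care at t1 and remain events at t3. Clinics differ only in b, with standard deviation s. The totals stay at 15% and 25%, so new uptake among non-users is u = (p − b)/(1 − b). The clinic variance of the outcome is v = [s(1 − u)]² and the ICC is v / [p(1 − p)].

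Example with b = 10%, s = 5 points:

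- control: u = 0.05/0.90 = 0.0556; v = (0.05 × 0.9444)² = 0.00223; ICC = 0.00223/0.1275 = 0.0175
- intervention: u = 0.15/0.90 = 0.1667; v = (0.05 × 0.8333)² = 0.00174; ICC = 0.00174/0.1875 = 0.0093
- variance of one clinic's proportion, [p(1 − p) − v]/50 + v: 0.00474 (control), 0.00545 (intervention)
- 308/50 = 6.16 clinics per arm: SE = √[(0.00474 + 0.00545)/6.16] = 0.0407
- power = Φ(0.10/0.0407 − 1.96) = 69%

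| Assumed t1 use | Between-clinic SD | Control-arm ICC | Power |
|---|---|---|---|
| 5% | 1.25 points | 0.001 | 87% |
| 5% | 2.5 points | 0.004 | 83% |
| 5% | 5 points | 0.016 | 71% |
| 10% | 2.5 points | 0.004 | 83% |
| 10% | 5 points | 0.0175 | 69% |
| 10% | 10 points | 0.070 | 39% |

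These powers are upper bounds. They allow no other source of clinic variance, use a normal reference with only 13 clinics, and treat all 616 patients as evaluable although the endpoint concerns distressed patients.

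**4. What adjustment could recover.** Assume that t1 use explains 36% of the between-clinic variance (a clinic-level correlation of 0.6, which has no source in the article). At the planned ICC, 0.005 × 0.64 = 0.0032, the design effect is 1.157, and power moves from 80% to 83%. At ICC 0.03, the lower end of the range quoted from the comparable trial, 0.03 × 0.64 = 0.0192, the design effect is 1.94, and power moves from 51% to 61%. Most of the larger gain comes from the higher ICC, which is a separate question.

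**The case against.** The strongest reply is that the premise is inferred. The t3 instrument is described as adapted, and the adaptation may limit recall to care since t1; an article can leave that wording to the full protocol. This stands as a caveat on whether prior care is counted. It does not remove the case for the covariate, since t1 use would probably predict later uptake either way.

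Second, the trial aims to compare how many distressed patients receive adequate care, and a patient already in care fits that aim. This stands too, and is why newly started care belongs in a supporting analysis and not in a redefined primary endpoint.

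Third, disease stage and time since diagnosis are already adjusted for and partly stand in for earlier contact with services. That is fair, but they are indirect substitutes for something measured directly.

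Three stronger readings are tempting and unsupported:

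- **Dilution of the effect.** A reader might take 20% of patients as already in care and turn 15% vs 25% into 32% vs 40% (0.20 + 0.80 × 0.15 and 0.20 + 0.80 × 0.25). That treats 15% and 25% as new uptake. If all care counts, the article's 15% already contains continuing prior care, so at most 15% of control patients could be such users. If only new care counts, prior care is not an event.
- **Bias.** At a 20% rate, ICC 0.03 and an assumed 6/7 split of clinics, the chance difference between arms has SD √(0.03 × 0.16) × √(1/6 + 1/7) = 3.9 points, or about ±7.5 points. This is ordinary cluster variation that the random intercept allows for. At ICC 0.005 the SD is 1.6 points.
- **A required clinic-level covariate.** Adding each clinic's t1 proportion costs a degree of freedom among 13 clinics. It is also open to influence from allocation, because the trial is unblinded and enrolls for about two years.

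**Conclusion.** The point holds as one of precision. Three facts are in the text: t1 use is collected, it is missing from an explicit covariate list, and nothing stated restricts the outcome to care begun after the consultation. No systematic bias follows. The loss could be negligible if prior use is rare or similar across clinics. It could be material if clinics differ by several points, as the assumed cases show (power 87% down to 39%). The article does not allow a single figure. The change is worth making before analysis because the data are already in hand, and adding the covariate afterwards would look post hoc.

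**What to change.** In Statistical analysis, add patient-level use of psychosocial support at t1 (yes/no) to the covariates of the primary random-intercept model. Prespecify one supporting analysis that counts only care newly started after the t1 consultation. State whether the t3 questionnaire asks about any care or only care since t1.

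The cost is a few sentences and one more patient-level covariate; no visit, form or recruitment target changes. There is one small risk. In an unblinded cluster trial, clinics allocated to the intervention may change their general practice, so the t1 use of patients enrolled later could be slightly affected by allocation, and adjusting for it could remove a little of the effect. For that reason, also report the primary model without t1 use.
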